### Population

2.2

Participants recruited into the study need to fulfill the following criteria: clinical diagnosis of COPD and symptoms indicative of exacerbation; spontaneous breathing on hospital admission; and physiotherapy since the first day of hospitalization. The exclusion criteria are as follows: patients who are uncooperative, those have previous thoracic surgery, thoracic deformities or any condition that make it difficult to apply the KT, and those with reports of allergic skin reactions to the use of adhesive bandages, plasters, or other adhesive materials.

### Random and blind

2.3

Before starting the study, a randomization list is produced using software-generated randomized numbers; the randomization depends on random blocks of 10. Patients will not know to which group they are assigned or which treatment they will be offered. Patients will be assigned at random to the COPD medical treatment + KT (Group 1), or the COPD medical treatment alone (Group 2). Participants are enrolled by the research assistant. After baseline examination, all patients will be given a full explanation of the treatment protocol and will be required to sign a written informed consent for study participation and for publication of the results. All the data collectors, doctors, statistical analysts, as well as result assessors are not aware of grouping assignment (Fig. 1).

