### Intervention protocol

2.4

In Group 1, KinesioTex Gold is used for KT application. Patients are seated on a chair. When the patients are at the end of the expiration, it will be applied bilaterally on the fifth to sixth and ninth to tenth intercostal muscles transversally and on the anterior and posterior axillary line longitudinally with 50% tension. To stimulate the muscle and support the function, the stimulation technique is usually applied from the origin to the insertion of the muscle with the recommended stretching of 25 to 50%. KT is changed on every fifth day (for a total of 3 times and 15 days) by the same certified physiatrist who has previously attended the KT training course. The patients are instructed not to take the tapes off at any time but they are allowed to take showers. The researcher, who is blind to the type of treatment, completes posttreatment (15th day) evaluations for each patient and recorded the data.

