## Discussion

3

The purpose of medical treatment of COPD is to reduce the frequency and severity of the symptoms and to improve the functional capacity and the quality of life. To our knowledge, only 1 study has investigated the effects of KT on pulmonary function and functional capacity of patients with COPD. Therefore, there is still a lack of high-quality evidence to prove the effectiveness of KT for COPD patients. In this study, our purpose was to investigate the effect of KT on respiratory function and muscle strength in the COPD patients who were in stable condition. It was hypothesized that thoracic KT could significantly change pulmonary function and functional capacity in patients with COPD. In our protocol, a total of 120 subjects will be recruited.

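### A single published block size of 10, with tape against no tape and no sham described, could make up to about 20 of 120 allocations certain to an enroller who sees earlier assignments

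*Protocol article*

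**What the plan says.** All references are to the protocol article.

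- **List and block size.** Section 2.3 (Random and blind) says that before the study starts "a randomization list is produced using software-generated randomized numbers", and that "the randomization depends on random blocks of 10". No second block size and no random variation of size is mentioned.
- **Enrolment.** The same section says: "Participants are enrolled by the research assistant".
- **Arms.** Both arms receive medical treatment for COPD. Group 1 also receives kinesio taping, and no sham tape is described for Group 2.
- **Blinding of staff.** "All the data collectors, doctors, statistical analysts, as well as result assessors are not aware of grouping assignment". The research assistant is not named in that list.
- **Blinding of patients.** "Patients will not know to which group they are assigned or which treatment they will be offered".
- **What the tape involves.** Section 2.4 (Intervention protocol) places tape on both sides of the thorax for 15 days, changed every fifth day by a physiatrist. It adds: "The patients are instructed not to take the tapes off at any time but they are allowed to take showers".
- **Exclusions.** Section 2.2 (Population) excludes, among others, uncooperative patients and those with any condition that would hinder taping.
- **Sample size.** The Discussion says that "a total of 120 subjects will be recruited".

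**The concern.** In a permuted block of known size, anyone who has counted the assignments so far knows how many of each arm remain. Near the end of a block the next assignment is sometimes certain, and the last one always is. This matters only if earlier assignments can be learned. Here the two arms differ by tape on the patient's chest with nothing to imitate it, so learning them is plausible.

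The exclusion criteria give room to act on such knowledge. Whether a patient is uncooperative, or hard to tape, is a judgement, and the second criterion concerns the treatment of one arm only. An enroller who expects tape next might apply it differently from one who expects control. Spirometry and maximal respiratory pressures depend on effort, so selection on cooperativeness would bear directly on the outcomes. Bias that enters at enrolment cannot be fully repaired in the analysis.

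**Working it through.** The article gives no predictability figure, so there is nothing of its own to reproduce beyond the block count: 120 / 10 = 12 complete blocks.

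**Inputs from the article:** block size 10 (section 2.3); 120 patients (Discussion); two arms (section 2.3).

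**Assumptions not in the article:** 1:1 allocation, so 5 + 5 in each block; one unstratified list; an enroller who knows every earlier assignment in order. The stated wording is read as permuted blocks of constant size 10.

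**1. Places known with certainty.** For a block of 2m places the expected number is 2m / (m + 1).
- With m = 5: 10 / 6 = 1.67 per block.
- Over 12 blocks: 12 × 1.67 = 20 of 120, or 16.7%.
- The chance that at least the last k places are known is 2 × C(10 − k, 5) / C(10, 5). For k = 1 this is 100%, for k = 2 it is 44.4%, and for k = 3 it is 16.7%.

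**2. Best-guess hit rate.** The strategy is to guess the arm with more places left. Expected correct guesses per block are 5 + (2^10 / C(10, 5) − 1) / 2 = 5 + (1024 / 252 − 1) / 2 = 6.53. That is 65.3%, or 78.4 of 120, against 60 by chance.

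**3. What acting on it could do.** Suppose the enroller shifts mean prognosis by +d when tape is expected and by −d when control is expected.
- Acting on certain places only: the spurious group difference is about 2d × 20 / 120 = 0.33d.
- Acting on every best guess: about 2d × (2 × 0.653 − 1) = 0.61d.

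The article gives nothing from which d could be estimated.

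**4. Other fixed sizes, certain places in 120.**

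| Block size | Certain places |
|---|---|
| 4 | 40 |
| 6 | 30 |
| 8 | 24 |
| 10 | 20 |

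**5. Varying sizes.** Lists of 120 were simulated against an optimal guesser who knows the set of sizes but not their order.

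| Scheme | Certain places in 120 | Best-guess hit rate |
|---|---|---|
| Fixed 10 | 20.0 | 65.3% |
| 6, 8, 10 | 1.9 | 66.3% |
| 8, 10, 12 | 1.6 | 65.0% |
| 6, 8, 10, 12 | about 1 | about 65.5% |

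Varying the size almost removes certainty. It does not reduce better-than-chance guessing.

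**The case against.** The strongest reply is that the article nowhere says the enroller learns earlier assignments. The tape is on the chest, so how visible it is to the research assistant is an inference. Section 2.3 also claims blinding of patients, data collectors, doctors, analysts and assessors. This stands in part: knowledge of past assignments must remain a condition of the point and cannot be stated as fact. The blinding claim does not dispose of it, though. It does not name the person who enrols, and it is hard to sustain with continuously worn tape, no sham, and a physiatrist who has to know whom to tape.

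Three further replies stand.

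- Ten is the least predictable of the fixed sizes compared above, so it is not a poor choice among them.
- The 65.3% and the 20 of 120 are upper bounds that fall if the enroller knows only some earlier assignments. A reader might infer that recruiters can generally foresee the next allocation. Even in the worst case about five assignments in six are not certain, and the best guess is right about two times in three.
- A reader might infer that allocation concealment is missing. The article condenses a fuller protocol, and details such as who holds the list or how assignments are released may be given there. Their absence here is not an error.

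**Conclusion.** The point holds as a conditional risk created by a stated design choice: one block size, now public, in a trial whose treatment is hard to hide. Its size is up to about 20 of 120 assignments known with certainty before enrolment. This rests on 1:1 allocation, one unstratified list and an enroller who follows earlier assignments in sequence.

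The article does not support the stronger conclusion that selective enrolment takes place, or that the results will be biased by a given amount; it shows the opportunity only. Nor does it contradict itself on block size, since 120 patients fill 12 blocks exactly. The change is worth making because it is nearly free and removes almost all of the certainty.

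**What to change.** Before the first patient, or for the remaining places if recruitment has begun, regenerate the list with randomly varying block sizes (for example 6, 8, 10 and 12) that are not disclosed to enrolling staff. Remove the fixed size from documents used at the site. If the block size already varies, correct the wording of section 2.3.

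Because guessing stays near 65% under any of these mixes, also keep the list and past assignments from the research assistant as far as possible. If the full protocol already arranges this, a short statement that it covers the enroller is enough.

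The cost is one new list and a possible imbalance of a few patients at the end, because the last block may be incomplete. With a largest block of 12 the two arms can differ by at most 6.

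### Section 2.3 claims that patients and all doctors are blind, which a comparison of chest tape with no tape cannot deliver; assessor blinding is feasible, but the article does not say how it is protected

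*Protocol article*

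**What the plan says.** Section 2.3 (Random and blind) makes two claims about blinding. For patients: "Patients will not know to which group they are assigned or which treatment they will be offered". For staff: "All the data collectors, doctors, statistical analysts, as well as result assessors are not aware of grouping assignment".

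The same section sets out the comparison: "Patients will be assigned at random to the COPD medical treatment + KT (Group 1), or the COPD medical treatment alone (Group 2"). It also says that, after the baseline examination and before written consent, "all patients will be given a full explanation of the treatment protocol".

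Section 2.4 (Intervention protocol) describes the tape in Group 1. It is "applied bilaterally on the fifth to sixth and ninth to tenth intercostal muscles transversally and on the anterior and posterior axillary line longitudinally". It is changed every fifth day, three times over 15 days, "by the same certified physiatrist who has previously attended the KT training course". On wear, "The patients are instructed not to take the tapes off at any time", although showers are allowed. A researcher described as blind to treatment type does the day-15 evaluation.

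Section 2.5 (Outcome measure) names the outcomes as pulmonary function by spirometer and respiratory muscle strength as MIP and MEP. The Discussion gives a total of 120 subjects.

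**The concern.** The blinding statement describes a property that the design does not have. A patient who has been told what the trial compares, and who does or does not have tape on the chest, knows the group. A physiatrist who puts the tape on knows it too.

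This matters because of the outcomes. Forced spirometry, MIP and MEP each require the patient to push as hard as possible, so motivation and encouragement can affect the reading. With no sham, a difference between the arms may contain an expectation component as well as any effect of the tape. That is a tolerable limitation if it is declared. If the report repeats section 2.3, readers and later risk-of-bias assessments will treat that component as excluded by design.

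**Working it through.** The core of this point is consistency between sections, so the claims are taken one group at a time.

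**Patients.** Claim (2.3): they know neither group nor treatment. Against it: the comparator is medical treatment without tape (2.3); the treatment protocol is explained in full to everyone (2.3); Group 1 has strips on both sides of the chest for 15 days and is told to leave them on (2.4); no sham is described. The claim cannot be true for either arm. The number affected is all 120 of 120.

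**Doctors.** Claim (2.3): all are unaware. Against it: a physiatrist, who is a doctor, applies and changes the tape (2.4). The claim fails for that person at least. It could still be true of doctors who take no part in taping, although one who examined the chest would see any tape.

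**Outcome assessor.** Claim (2.3 and 2.4): blind. Nothing in the article contradicts this. The evaluator is described as a separate blind researcher, the tape sites can lie under clothing, and the tests are done seated. The weak points are that patients who know their group can mention it, and that the article does not say whether tape is on during day-15 testing.

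**Statistical analysts.** Claim (2.3): blind. This is feasible, and no passage conflicts with it.

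**Illustration of what expectation could do.** No figure in the plan can be reproduced here: the article gives the total of 120 without an effect size, standard deviation (SD) or power. Assumptions that are not in the article: 60 per arm (1:1), a two-sided test at 0.05, a normal approximation, no true tape effect, and an effort difference of b SD between arms.

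- Standard error in SD units: √(2/60) = 0.1826.
- P(reject) = 1 − Φ(1.96 − b/0.1826) + Φ(−1.96 − b/0.1826).
- Example, b = 0.2: 0.2/0.1826 = 1.095, so P = [1 − Φ(0.865)] + Φ(−3.055) = 0.1937 + 0.0011 = 0.1948.

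| Assumed b (SD) | False-positive rate per outcome |
|---|---|
| 0 | 5.0% |
| 0.1 | 8.5% |
| 0.2 | 19.5% |
| 0.3 | 37.6% |
| 0.4 | 59.1% |
| 0.5 | 78.2% |

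For scale, the difference detectable with 80% power is (1.960 + 0.842) × 0.1826 = 0.51 SD. The rates are the same whichever arm the bias favours, because the test is two-sided. The values of b are chosen for illustration, and nothing in the article supports one over another.

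**The case against.** **The patient sentence may mean concealment before assignment.** It stands between the randomization list and the assignment sentence and speaks of treatment still to be offered. This reading is possible. However, the section heading covers blinding as well as randomization, and the sentence is not limited to the time before assignment. On that reading it would still need rewording, and the conflict over doctors would remain.

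**Doctors may mean study doctors other than the one who tapes.** That may be the intention, but the sentence says all. A short qualification settles it.

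**An article leaves detail to the full protocol.** This is right for how assessor blinding is maintained, so silence on that is not counted as an error here. It does not help the patient claim, which is a positive statement that the article's own comparator contradicts.

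**A comparison without sham is legitimate.** Agreed. The fault lies in the description of the trial.

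**Measurement rules limit submaximal effort.** Spirometry takes the best of three attempts. MIP and MEP follow named society standards, with manoeuvres agreeing within 20%. These rules may reduce the scope for poor effort. They do not remove the influence of expectation.

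**A stronger reading that the documents do not support.** A reader might infer that the assessor is unblinded too, on the ground that the tape is visible and never comes off. The article does not say that the tape is visible during testing. The instruction not to remove it is addressed to patients, while staff change it, and three five-day applications end at about day 15. Assessor blinding is therefore unprotected in the text, but not shown to be false.

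**Conclusion.** The point holds for patients and for the taping physiatrist: section 2.3 is wrong as written and should be corrected. It affects all 120 planned participants and rests only on the article's own description of the two arms, not on any assumption about effect sizes.

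For the assessor the finding is narrower. Blinding is asserted and feasible, but open to disclosure by patients who know their group. Analyst blinding is not in question.

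A reader might also infer that the bias must favour the tape, or that it amounts to a definite share of the detectable difference. The documents support neither inference. Size and direction are unknown, and the illustrative rates depend on an assumed bias, 1:1 allocation and two-sided testing; the 0.51 SD benchmark further assumes 80% power. They show only that a modest effort difference would not be negligible in a trial of this size.

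**What to change.** In section 2.3, delete the claim that patients are blind and limit the claim for doctors to those not involved in taping. Describe the trial as open-label for patients and the taping physiatrist, with blinded outcome assessor and statistician.

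Protect the assessor's blinding at day 15:

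- cover the chest in the same way in both arms, which works whether or not tape is on;
- tell patients not to mention tape to the tester;
- use a fixed coaching script for all manoeuvres;
- use a tester who takes no part in taping.

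These steps protect the assessor and do nothing about patient expectation. The protocol and the report should therefore state that patients were unblinded and the outcomes depend on effort, as a limit on the conclusion. A sham-tape control would be a larger change of design and is not needed to correct the statement.

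The cost is a less favourable blinding statement, a few sentences of protocol text, and minor work at the day-15 assessment.

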**Figure 1 F1:**
[figure not shown]
PRISMA flow diagram describing the selection process for relevant clinical trials used in this meta-analysis.

### Intervention protocol

2.4

In Group 1, KinesioTex Gold is used for KT application. Patients are seated on a chair. When the patients are at the end of the expiration, it will be applied bilaterally on the fifth to sixth and ninth to tenth intercostal muscles transversally and on the anterior and posterior axillary line longitudinally with 50% tension. To stimulate the muscle and support the function, the stimulation technique is usually applied from the origin to the insertion of the muscle with the recommended stretching of 25 to 50%. KT is changed on every fifth day (for a total of 3 times and 15 days) by the same certified physiatrist who has previously attended the KT training course. The patients are instructed not to take the tapes off at any time but they are allowed to take showers. The researcher, who is blind to the type of treatment, completes posttreatment (15th day) evaluations for each patient and recorded the data.

### Outcome measure

2.5

The outcome measures are pulmonary function and respiratory muscle strength. Pulmonary function was measured using a spirometer. To perform the measurement, subjects were instructed to sit on an armless chair with back support while their knees flexed to 90° and nostrils occluded by a nose clip. Then they performed a maximal inspiration followed by a forced expiration, exhaling as much air as possible 3 seconds. This maneuver was repeated 3 times, and the highest scores were recorded for analyses. Respiratory muscle strength will be measured as maximum inspiratory pressure (MIP) and maximum expiratory pressure (MEP), using an analogic manovacuometer. The assessments are performed in accordance with American Thoracic Society/European Respiratory Society standards (2002). The participants are assessed in the seated position. The MIP maneuver begins near residual volume, and the MEP maneuver begins near total lung capacity. The maximum score of 3 maneuvers varying by less than 20% will be recorded.

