### Statistical analysis

2.6

All analyses will be performed using SPSS for Windows, version 16, and GraphPad InStat. Analysis of variance is used for comparing mean values of patient's age, weight, height, and body mass index. For nonparametric measures, differences between baseline and posttreatment scores for each group are computed by the Wilcoxon signed ranks test. The difference between each treatment group is performed by the Kruskal–Wallis test. The level of statistical significance is set as *P* < .05.

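### No primary endpoint is named: at least three co-equal measures share one unadjusted 5% level, so the chance of some false-positive difference is roughly 10–26% if three to six are tested

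*Protocol article*

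**What the plan says.** Section 2.5 (Outcome measure) of the protocol article opens with "The outcome measures are pulmonary function and respiratory muscle strength". The two families stand side by side, and neither is called primary or secondary.

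- **Muscle strength** is defined as two variables: "Respiratory muscle strength will be measured as maximum inspiratory pressure (MIP) and maximum expiratory pressure (MEP), using an analogic manovacuometer".
- **Pulmonary function** has an instrument but no variable: "Pulmonary function was measured using a spirometer". The description of the maneuver ends with "This maneuver was repeated 3 times, and the highest scores were recorded for analyses". The plural does not settle how many spirometric values will be compared.

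Section 2.6 (Statistical analysis) gives one between-group method for the outcome scores: "The difference between each treatment group is performed by the Kruskal–Wallis test". Within each arm, "differences between baseline and posttreatment scores for each group are computed by the Wilcoxon signed ranks test". It then states "The level of statistical significance is set as *P* < .05". It does not say whether that level applies per test or to the whole set, and it gives no hierarchy or adjustment.

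The Introduction and Discussion do not identify a deciding variable either. The stated purpose concerns respiratory function and muscle strength. The stated hypothesis concerns pulmonary function together with functional capacity. Functional capacity has no measure in section 2.5, and muscle strength is not in the hypothesis.

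**The concern.** A trial with one pre-named deciding variable tested at two-sided 0.05 has a 5% chance of declaring a difference when there is none. If several variables share that role, each at the full 5%, the chance that at least one crosses the line is higher. The protocol then gives no rule for which result answers the trial's question. A reader of the final report could not tell whether a significant MIP, a significant MEP or a significant spirometric value was the planned test or the most favourable of several. The stated 5% would not describe the error rate of the trial's conclusion.

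**Working it through.** **Inputs from the document**

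- Level: 0.05 (section 2.6). Kruskal–Wallis on two groups is non-directional, so this is a two-sided level.
- Groups: two (section 2.3).
- Time points: one post-treatment assessment, day 15 (section 2.4), so repeated visits add no multiplicity.
- Muscle-strength variables: two, MIP and MEP (section 2.5).

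**Assumptions, because the document gives no figure**

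- Spirometric variables: m = 1 to 4, so k = m + 2 = 3 to 6 between-group tests. Since m must be at least 1, k = 3 is the minimum.
- Correlation between test statistics: 0 to 0.9. Measures on the same patient are likely to be positively correlated, so for a given k the independent case is close to an upper value.
- Each variable is tested at 0.05. This is the natural reading of a single unqualified level.
- The within-arm Wilcoxon tests are not counted.

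**The plan's own figure.** The plan states no familywise error rate, so there is nothing to reproduce beyond the 5% for one test. A simulation of Kruskal–Wallis with two groups of 60 (120 split equally) gave a rejection rate of 0.050, so the single test holds its level.

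**Step 1. Independent tests, either direction: 1 − 0.95^k**

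- k = 3: 1 − 0.8574 = 14.3%
- k = 4: 1 − 0.8145 = 18.5%
- k = 5: 1 − 0.7738 = 22.6%
- k = 6: 1 − 0.7351 = 26.5% (26.49% before rounding)

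**Step 2. Independent tests, difference favouring KT only: 1 − 0.975^k**

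This gives 7.3%, 9.6%, 11.9% and 14.1% for k = 3, 4, 5 and 6. For one test it is 2.5%.

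**Step 3. Correlated tests.** These come from simulation of equicorrelated normal test statistics, 1,000,000 draws per setting, each tested at two-sided 0.05. Each cell shows either direction / favouring KT.

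| Tests k | r = 0.5 | r = 0.7 | r = 0.8 |
|---|---|---|---|
| 3 | 12.6% / 6.3% | 10.9% / 5.5% | 9.9% / 5.0% |
| 4 | 15.5% / 7.8% | 13.1% / 6.5% | 11.4% / 5.7% |
| 5 | 18.3% / 9.2% | 14.8% / 7.4% | 12.7% / 6.3% |
| 6 | 20.7% / 10.3% | 16.5% / 8.2% | 13.8% / 6.9% |

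**Step 4. Block correlations.** With 0.7–0.9 among spirometric values, 0.5–0.7 between MIP and MEP, and 0.3–0.4 across families, the either-direction rate runs from 12.3–13.3% (k = 3) to 16.0–20.1% (k = 6). The rate favouring KT runs from about 6% to about 10%.

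**Step 5. Mildest case computed.** With k = 3 and r = 0.9 the rates are 8.4% in either direction and 4.2% favouring KT, still above 5% and 2.5%.

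**The case against.** The strongest reply is that this is a condensed article. A fuller protocol or a statistical analysis plan may exist, and the multiplicity procedure and order of testing are commonly placed there. That stands for the adjustment method. It does not stand for the primary outcome: designating it is protocol content, and this article has a dedicated outcome section that specifies seating posture and a nose clip but not the spirometric value to be compared. An analysis plan refines a primary endpoint, and here there is none to refine.

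Four stronger readings are tempting, and the document does not support them.

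- **That a false finding of benefit has a 15–26% chance.** Rates of that size count differences in either direction, including KT appearing harmful. In KT's favour the highest value computed is 14.1%, which needs six independent tests, and the comparator is 2.5%, not 5%. A floor of 15% would also leave out k = 3.
- **That any one significant measure would count as success.** No such rule is written. The hypothesis joins pulmonary function and functional capacity with *and*. The rates above are the chance of at least one false positive, not the error of a declared decision rule.
- **That the deciding variable will be picked after the data are seen.** The text leaves that open but does not show that it is planned.
- **That MIP is the obvious primary.** The taping rationale points to muscle stimulation, but the hypothesis puts pulmonary function first and omits muscle strength.

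How the 120 patients were arrived at is a separate sample-size question, and nothing here depends on it.

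**Conclusion.** The point holds: no primary endpoint is designated, the spirometric variables are unnamed, and at least three measures share one unadjusted 5% level. With three to six tests, the chance of at least one false-positive difference is 14–26% if they are independent and about 10–21% at correlations of 0.5–0.8, rather than 5%. For a difference favouring KT it is about 5–14% over the same settings, rather than 2.5%.

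The direction is firm, since both rates exceed their single-test values in every setting computed. The exact size is not firm. It rests on an assumed number of spirometric variables, assumed correlations, and reading P < .05 as applying to each test.

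**What to change.** Before unblinding, amend section 2.5 to name one primary variable at day 15 that matches the stated hypothesis. One named spirometric value would do so. MIP would serve if the hypothesis is revised to concern muscle strength. In section 2.6, state that this variable alone is compared between groups at two-sided 0.05 and that the efficacy conclusion rests on it alone. The error rate for the primary claim is then 5.0% in either direction and 2.5% in KT's favour.

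Name the remaining spirometric values, MIP and MEP as secondary. Test them in a fixed order or with Holm's procedure, or label them exploratory.

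If the sponsor prefers to keep all measures co-equal, Bonferroni per-test levels of 0.0167, 0.0125, 0.0100 or 0.0083 (0.05/k for k = 3 to 6) hold the familywise error at or below 5%, at a price in power. As an illustration, take a comparison of two means with 60 per group and an assumed standardised difference of 0.5: power falls from about 78% at 0.05 to about 63% at 0.0167.

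The recommended change costs only protocol and analysis-plan wording. Its small downside is that secondary results carry less weight.
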